### Outcome assessment

Standardised questionnaires will be used to measure the primary and secondary outcomes. Our choice of outcome measures is based on two previous trials of our working group to evaluate effectiveness of different interventions in the management of clbp [38,46]. They are also in line with international recommendations [47-50]. All outcomes measures and their measuring time are shown in Table 3.

**Table 3 T3:** Primary and secondary outcomes

**Domain/outcome**	**Questionnaire/items**	**Assessment time point**				**Reference**
**Primary Outcome**		t1	t2	t3	t4	
**Physical functioning**	Hannover Functional Ability Questionnaire (FfbH-R)	x	x	x	x	[51]
**Secondary Outcomes**						
**Pain**						
Pain intensity	Numeric Rating Scale (NRS)	x	x	x	x	[52]
Pain status	Graded Chronic Pain Status (GCPS)	x	x	x	x	[53]
**Physical activity**	Freiburg questionnaire on physical activity (FFkA)	x		x	x	[54]
**Emotional functioning**						
Depression	Patient Health Questionnaire (PHQ-D)	x	x	x	x	[55]
Anxiety	Generalized anxiety disorder 7-item scale (GAD-7)	x	x	x	x	[56]
**Health related quality of life**	Short-Form-12 (SF-12)	x	x	x	x	[57]
**Stress**	Perceived Stress Scale (PSS)	x	x	x	x	[58]
**Pain related cognitions, emotions and behavior**						
Cognitive and behavioral pain coping strategies	Pain Management Questionnaire (FESV)	x	x	x	x	[59]
Fear-avoidance and endurance-related responses to pain	Avoidance-Endurance Questionnaire (AEQ)	x	x	x	x	[60]
Pain related fear	Tampa Scale for Kinesiophobia (TSK)	x	x	x	x	[61,62]
**Motivational and volitional determinants of physical activity**						
	risk perception (3 items), self-efficacy (3 items), outcome expectancies (11items), experiences with physical activity (5 items), self-concordance (12 items), intention (7 items), action (4 items) and coping (4 items) planning, action control (6 items)	x	x	x	x	[63-67]
Stage of change algorithm for physical activity	two Items (Have you performed moderate physical for 30 minutes or longer on a minimum of 3 days per week? and "Since when are you as regularly active as you are now?"; possible answers: 1. Question: no, and I don’t intend to do so; no, but I am thinking about doing so; no, but I have the strong intention to do so; yes, but it is difficult to me; yes, and it is easy for me; 2. Question: open)	x	x	x	x	[68,69]
**Attitudes towards performing physical activity**	modified Version of Short-Questionnaire to measure cognitive and affective attitudes toward sports activities	x	x	x	x	[70]
**Treatment satisfactions with exercise therapy**	18 items (e.g. “I would recommend the exercise therapy other patients.” measured by using a six-point ordinal scale with 1= “absolutely agree”, 6=“absolutely disagree”; e.g. “The time extent of the exercise therapy, I perceived as…” measured by using a five-point ordinal scale with 1=“far too high“, 5=“far too low“; e.g. “Overall, how do you rate the exercise therapy?” measured by using a six-point ordinal scale with 1= “very satisfied”, 6=not “satisfied at all”)		x			self-designed
**Treatment satisfactions with the rehabilitation process**	five items (e.g. “Overall, how do you rate the rehabilitation process?”) measured by using a ten-point ordinal scale (1= “very poor”, 10 = „excellent“)		x			self-designed
**Others**						
Demographic characteristics	sex, age, height, nationality, marital status, education, monthly income, weight, self-reported work status	x				[71]
Social medical characteristics	a) self-reported low back pain related sick leave, use of health care services, medication use for the last six month and self-reported plan to apply for retirement, severe disabilities	x				[71]
	b) diagnosis, work status and physical capability taken from the hospital discharge report		x			
Aftercare	a) aftercare recommendations taken from the hospital discharge report		x			self-designed
	b) self-designed; five items (e.g. “Have you participated in the last twelve months in a medically prescribed exercise therapy to rehabilitation aftercare?” with the option to answer yes/no)				x	
Job satisfaction	scale on job satisfaction (IRES-3)			x	x	[72]

#### Primary outcome measure

We will use the level of functional limitations associated to clbp twelve months after the end of BMR measured by the Hannover Functional Ability Questionnaire (FFbH-R) as our primary outcome [51]. The FFbH-R consists of twelve items with a three-stage answering scale. Its summary score describes the low back pain associated functional ability in activities of daily living in adults on a scale of 0% (minimum functional ability) to 100% (maximum functional ability). The questionnaire is constructed for response to already light and moderate functional restrictions. The average item intercorrelation amounts to 0.50. The test-retest-reliability with repeated measures after approximately one week is above 0.75, Cronbach alpha figures 0.90 [51]. The one factorial structure of the instrument was confirmed in a principal component analysis. The FFbH-R is comparable to the internationally used Roland Morris Questionnaire for measuring clbp related disability with a correlation of 0.75 [73].

#### Secondary outcome measures

Secondary outcome measures refer to demographics and related characteristics, pain, physical activity, health-related quality of life, depression, anxiety, stress, pain-related cognitions, emotions and behavior, motivational and volitional determinants of physical activity, attitudes towards performing physical activity, satisfaction with exercise therapy and satisfaction with the rehabilitation process (see Table 3).

### Data analysis

Data analysis is carried out following evaluation standards of experimental study designs with control groups, using descriptive methods as well as inferential statistics. An intention-to-treat analysis will be performed. In the case of dropouts and withdrawals, multiple imputation techniques will be used. Baseline differences in demographic as well as the primary and secondary outcomes data will be analysed using two-sample t-tests for parametric and Wilcoxon test for non-parametric distribution as well as Chi-Square test for nominal data. The testing of the hypotheses is conducted via comparison of changes in the intervention and the control group regarding the primary and secondary outcomes. For this purpose, a saturated 4x2-factorial linear mixed effects model in the process of all four assessment time points and two groups as fixed effects and intercept and slope as random effects is used whilst controlling for statistically significant differences at baseline [74]. Changes in outcomes over time are represented by their linear slopes. Because of the disparity between the duration of the inpatient rehabilitation phase (27 days on average) and the follow-up phase (12 months), separate slopes for these phases are estimated by a spline model. Primarily overall group differences are identified by a model comparing likehood ratio test of a hypothesized model incorporating interaction effects of group by time and a nested null model leaving out these interactions. Additionally the slopes of both groups can be compared in two phases whilst controlling for statistically significant differences at baseline. Furthermore, a post hoc analysis using similar mixed effects linear regression techniques is conducted to model effects of secondary outcomes onto the primary outcome to explore possible interactions.

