### Randomisation

The randomisation procedure of the participants takes place with an online-based randomisation feature. Therefore, we implement a central data base for electronic data recording which will be used in each of the two rehabilitation centres. An independent administration employee, who is not involved in the study, will use the online-based randomization feature within each rehabilitation centre to register eligible participants via a web application. After registration, the online-based randomisation feature automatically accomplishes the allocation to one of the treatment groups.This system has been developed in a prior study [38] and incorporates the existing national data protection regulations. Clear advantages of this procedure are a prompt randomisation and a concealment of the sequence of allocation. For sequence generation we use an “urn randomisation”-algorithm [39]. It has good statistical properties [40] and can be used to stratify by different criteria. In this study we stratify for “rehabilitation centre” with the two rehabilitation centres and “gender” with two categories. Additionally, a structural equality by chance concerning both sub-samples is ensured.

The randomisation process of patients will be planned together with the staff of the participating rehabilitation centres, especially the medical directors, administration staff, system administrator and those responsible for therapy planning in the rehabilitation centres during the phase of preparation and implementation. For the planning of the randomisation process, the implementation of the data base and the training of administration staff to handle the data base, the rehabilitation centres will be visit two to three times.

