### Sample size and power calculation

Thinking of the short-term effectiveness of both interventions, only small differences between groups and small effect sizes at the end of rehabilitation (t2) (d=0,3 or f(V)=0,15) are expected to be found [12,41,42]. Because of the minor long-term effects of the present usual care, medium effect sizes (d=0,5 or f(V)=0,25) are expected to be found at six and twelve months. This is in line with Friedrich and colleagues [43,44], who were able to show medium effect sizes regarding a reduction of disability when comparing a functional exercise therapy to an exercise therapy which contained additional motivational strategies (Disability Score: d~0,68). Sample power (Software: G-Power 3.0) concerning the primary outcome was approximated for an analysis of covariance at t4 with medium effect size of Cohen’s d=0,5, alpha error 5% and test power of 80%. This approximisation results in a sample size of at least 128 patients without missing values. Anticipating a dropout rate of 40%, it is necessary to include 214 patients (n=107 for each group).

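### Centre and gender stratify the randomisation but are not prespecified model terms, and the baseline-significance rule will usually leave them out

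*Protocol article*

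**What the plan says.** On allocation, the Randomisation section states: "For sequence generation we use an “urn randomisation”-algorithm", and then "In this study we stratify for “rehabilitation centre” with the two rehabilitation centres and “gender” with two categories". That gives four strata.

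On analysis, the Data analysis section describes a saturated model with "all four assessment time points and two groups as fixed effects" and "intercept and slope as random effects". Its one provision for other covariates is "whilst controlling for statistically significant differences at baseline", and the same condition is repeated for the comparison of slopes. The primary comparison of the arms is a "model comparing likehood ratio test of a hypothesized model incorporating interaction effects of group by time" against a nested model without those interactions. Neither centre nor gender is named in this section. Sex is among the demographic items in Table 3, so the baseline tests could reach it. Centre is not listed there.

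Two other sections use the 12-month time point. Primary outcome measure defines the outcome as functional limitation twelve months after rehabilitation. Sample size and power calculation says: "Sample power (Software: G-Power 3.0) concerning the primary outcome was approximated for an analysis of covariance at t4". The inputs given there are a standardised difference of 0.5, a 5% error level and 80% power.

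**The concern.** Stratified allocation makes the arms more alike on the strata than chance alone would. An analysis that omits prognostic strata leaves their variance in the error term and does not credit the balance, so factors used to allocate are normally included as model terms.

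The article does not simply leave this choice to a later document. It states a covariate rule, and that rule works against the stratification factors: the better the allocation balances centre and gender, the less likely either is to differ significantly between arms. Inclusion then depends on a baseline test that these factors will pass less often than a variable left to chance. At stake is some precision, and an adjustment set that is chosen from the data when it could be fixed beforehand.

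**Working it through.** **1. The plan's own figures.** Inputs from Sample size and power calculation: d = 0.5 (f = 0.25), alpha 5%, power 80%, ANCOVA at t4, 40% dropout. Two-sided testing is assumed, which is what the ANCOVA F test amounts to. With a noncentral F for two groups and one covariate, the smallest total giving at least 80% power is 128 (power 0.801). Then 128 / (1 − 0.40) = 213.3, rounded up to 214. Both figures reproduce.

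**2. A 12-month level comparison with the strata left out.** Let R² be the share of 12-month FFbH-R variance explained by centre and gender. The article gives no value, so R² is an assumption. With arms balanced within strata, the true variance of the arm difference is (1 − R²) times what the unadjusted analysis estimates. With 64 per arm, the noncentrality is 0.5 × √32 = 2.828, and:

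- SE too wide by 1/√(1 − R²) − 1
- true alpha = 2 × [1 − Φ(1.96/√(1 − R²))]
- power, strata out = Φ[(2.828 − 1.96)/√(1 − R²)]
- power, strata in = Φ[2.828/√(1 − R²) − 1.96]

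| Assumed R² | SE too wide | True alpha | Power, strata out | Power, strata in | Points lost |
|---|---|---|---|---|---|
| 2% | 1.0% | 4.8% | 81.0% | 81.5% | 0.5 |
| 5% | 2.6% | 4.4% | 81.4% | 82.7% | 1.3 |
| 10% | 5.4% | 3.9% | 82.0% | 84.6% | 2.6 |

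For example, at 10%: 1.96/0.9487 = 2.066, and 2 × [1 − Φ(2.066)] = 0.039. Power stays above the planned 80% in every row, so no stated number changes.

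**3. The planned group-by-time contrast.** Illustrative assumptions, none from the article: random-intercept SD 14, random-slope SD 0.5 per month, residual SD 9, t4 at 12.9 months from t1, 128 complete patients, random effects per patient, and time-constant effects of 6 points each for centre and gender. The strata then add 2 × 3² = 18 to the between-patient variance.

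- Arm difference at t4, strata out: variance per patient 196 + 18 + 0.25 × 12.9² + 81 = 336.6; SE = √(336.6 × 4/128) = 3.24.
- Arm difference at t4, strata in: 336.6 − 18 = 318.6; SE = √(318.6 × 4/128) = 3.16.
- Arm difference in change from t1 to t4: the intercept and the 18 both drop out, leaving 0.25 × 12.9² + 2 × 81 = 203.6; SE = √(203.6 × 4/128) = 2.52. A generalised least squares calculation over all four time points gives 2.52 with and without time-constant stratum terms.

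**4. Simulation under no effect.** In 20,000 runs with the same assumptions and exact balance within strata, the type I error at t4 was 0.044 with strata out and 0.051 with strata in. For change from t1 with strata out it was 0.051. These runs used ordinary least squares; the full mixed model was not simulated to completion. The result for the planned contrast therefore rests on the variance calculation and the change-score simulation.

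**The case against.** The strongest counter-argument is that the planned primary test compares changes, with t1 as a response and a random intercept. Stable differences between centres or sexes cancel there, as step 3 shows. This stands. A reader might infer that the primary test's standard errors are too wide for the design, but the documents do not support that. It would need change over time or dropout to differ by stratum. The article anticipates 40% dropout but says nothing about either by centre or gender, so the size of that effect is unknown.

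The figures in step 2 therefore describe a test that Data analysis does not plan; the ANCOVA at t4 appears only as the basis for sizing. That also stands, although the primary outcome is defined at 12 months. Even in an ANCOVA, baseline FFbH-R would already carry part of any stable stratum effect, so the added R² may be at the low end of the range. Urn allocation balances only approximately, which shrinks the mismatch further.

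It is also fair to say that centre has not been shown to be prognostic. Recruitment procedures describes different invitation and consent logistics at the two sites, but the control-arm description calls the two programmes conceptually similar, and no outcome difference is reported.

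Two other readings go too far. The model is not confined to time and arm, because the conditional covariate clause exists and could admit sex. Nor is the benefit of stratifying lost: the balance, and the smaller true sampling variance it brings, remain without adjustment. At most the estimated standard error fails to credit it.

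The objection does not rescue the covariate rule itself, which makes adjustment for the randomisation factors depend on a test that the randomisation is built to make non-significant.

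**Conclusion.** The point holds as a modest, nearly free improvement. The article names no stratification factor in its model and states a covariate rule that will usually exclude both. For the planned group-by-time test the expected effect is nil with complete data and time-constant stratum effects. For a 12-month level or ANCOVA-type comparison the effect is mild conservatism of the size in the table, under an assumed R² of 2 to 10% and exact balance within strata. A reader might infer inflated false positives or a wrong sample size. Neither follows: the error lies below 5%, and 128 and 214 both reproduce and need not rise.

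**What to change.** In Data analysis, state that centre and gender are fixed covariates in the primary and secondary models regardless of any baseline test. The form depends on the model:

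- If t1 stays a response, include centre-by-time and gender-by-time terms with their main effects. Main effects alone leave the group-by-time contrast unchanged.
- If t2 to t4 are modelled with baseline FFbH-R as a covariate (the baseline score of the outcome concerned for secondary models), include centre and gender as main effects.

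The cost is a sentence of text and a few degrees of freedom: two parameters in the second form, and 2 + 2 × 3 = 8 in the first with four categorical time points. Both variables are already needed for the stratified randomisation, so no new data and no extra patients are required.

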In both rehabilitation centres, the group size is limited to twelve participants. If the number of eligible study patients is too small for starting a control or intervention group, the participation of non-eligible patients who do not take part in the study is accepted to reach the necessary group size. At least 40 potentially eligible patients will be treated every month in both rehabilitation centres. Considering a recruitment rate of 60%, 358 eligible patients will have to be asked to participate in the study in order to achieve the required sample size. Based on the assumption that average closed groups consist of six to seven participants, the recruitment period is predefined as a period of twelve months. Both rehabilitation centres confirmed that a sufficient number of eligible patients would exist to achieve the necessary sample size in the study period.

The collection of consent forms, distribution and collection of questionnaires and the delivery of the latter to the study team are adjusted to the process of patient admission and discharge in standardised form. The process will be tested and automated in each of the rehabilitation centres during the phase of implementation.

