### Interventions

#### Control arm

Both of the participating rehabilitation centres have a conceptually similar BMR for patients with orthopedic functional impairment and concurrent substantial psychological or social component of this impairment. The behavioural medical concept takes into account the biopsychosocial mechanisms relevant for the chronification of musculoskeletal disorders [9,45]. Empowerment and self-management are encouraged. On average, the BMR lasts for 27 days. Compared to the traditional multidisciplinary inpatient rehabilitation, the BMR has specifically defined inclusion criteria [11]: 1) an interdisciplinary admission, 2) a standardized psychosocial assessment, 3) a reconciled interdisciplinary case management, 4) case reviews on a regular basis, 5) supervision, 6) closed groups (a group remains together in all treatments during their whole stay at the rehabilitation centre), 7) the possibility of an individually tailored rehabilitation schedule and 8) therapist consistency for the most part (a therapist accompanies a group throughout a whole intervention). The multiprofessional core of the BMR relies on psychological interventions and standard exercise therapy (SET), in which ten to twelve patients take part together as a closed group. Other interventions are presentations with information about health and health behavior, rehabilitation/social counseling and if necessary occupational therapy. The total extent of therapy during the stay in the rehab centre is 65 hours on average, including approximately 26 hours exercise therapy. An experienced orthopedist bears the overall responsibility. A detailed description of the psychological group and exercise therapy group is available in the Additional files (see Additional file 1).

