#### Intervention arm

Participants in the intervention arm will also receive a BMR, but with a specific behaviour-oriented exercise therapy (BET), which replaces SET. BET has been developed on the basis of previous work [46]. In general, BET aims at facilitating health-related knowledge and skills, which empower patients to maintain a healthy, physically active lifestyle beyond their BMR treatment. It’s based on the assumption that a theory-based, systematic and integrated targeting of relevant psychosocial factors in the chronification of low back pain and also determinants of health behavior change, as well as factors of physical deconditioning and disuse improves the self-management and therefore reduces functional impairment of patients with clbp. This is reached by a structured combination of exercise, education and behavioural elements with a strong emphasis on patients’ preferences and their previous experiences with exercise. Therefore different types of exercise are considered for patients to become familiar with their execution (e. g. methods of controlling intensities and training progression), as well as to encourage positive experiences with exercise. BET is delivered in closed groups with six to twelve patients during the approximately four weeks of the BMR. In total, exercise therapy comprised an extent of 26 hours on average. Both the fifteen sessions and the related modules of BET are guided by the same trained BET-therapist.

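### Patients are treated in closed groups, but the sample size and the mixed model treat them as independent: any positive within-group correlation makes the primary test too liberal and lowers power relative to the stated calculation

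*Protocol article*

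**What the plan says.** **Allocation.** The Randomisation section describes web-based allocation of individual patients, stratified by centre and gender.

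**Delivery.** The Control arm section lists among the features of the rehabilitation programme (BMR) "closed groups (a group remains together in all treatments during their whole stay at the rehabilitation centre". It also says that a therapist stays with a group for the most part. For the behavioural exercise programme (BET) this is explicit: the fifteen sessions and the related modules are "guided by the same trained BET-therapist". Recruitment procedures assumes that "average closed groups consist of six to seven participants" and caps groups at twelve. Patients outside the study may fill a group that is too small.

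**Sample size.** Power "was approximated for an analysis of covariance at t4", the twelve-month assessment, "with medium effect size of Cohen’s d=0,5, alpha error 5% and test power of 80" per cent. Then: "This approximisation results in a sample size of at least 128 patients without missing values". Then: "Anticipating a dropout rate of 40%, it is necessary to include 214 patients (n=107 for each group" arm.

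**Analysis.** Data analysis specifies a model with four time points and two arms in which "two groups as fixed effects and intercept and slope as random effects is used". The primary test is a likelihood ratio test of the interaction between arm and time. No ICC, design effect, or term for closed group or therapist appears anywhere in the article. The Treatment adherence and Discussion sections deal with contamination and treatment integrity, but not with clustering.

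**The concern.** Individual randomisation makes patients independent at baseline. It does not keep them independent once treatment is given in fixed groups. Members of one closed group share a therapist (at least for most of the stay), a group climate and an arrival date, and their later outcomes can be alike for those reasons. Each closed group belongs wholly to one arm, so variation between closed groups adds to the variance of the difference between arms.

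The article does not name the level of the random intercept and slope. With repeated questionnaires the natural reading is the patient. A patient-level term separates patients from one another, but it does not take up variation shared by a whole closed group. The shared effect begins after baseline, so it enters change over time, which is what the interaction test examines.

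At stake is the validity of the primary p-value. The same model serves the secondary outcomes, so they are affected in the same way.

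**Working it through.** **Reproducing the plan's figure.** The inputs are d = 0.5 (f = 0.25), alpha 0.05 two-sided and one numerator degree of freedom, from the sample size section. Sidedness is not stated, but only the two-sided version fits (one-sided gives 100). The noncentral F calculation for an analysis of covariance gives N = 128 with power 80.1%. Inflating for 40% loss gives 128 / 0.60 = 213.3, rounded up to 214. Both stated numbers reproduce exactly with a design effect of 1, so no allowance for clustering is built in.

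**Number and size of closed groups.** Taking 6.5 as the midpoint of six to seven, 214 / 6.5 = 32.9, or about 33 closed groups and roughly 16 per arm. With 40% loss, 6.5 × 0.60 = 3.9 completers per closed group. This is the size consistent with the plan's own 128 evaluable patients.

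**Formulas.** The ICC is that of the twelve-month outcome on the scale analysed.
- Design effect: DE = 1 + (m − 1) × ICC, with m = 3.9.
- Effective sample size: 128 / DE. Power comes from the noncentral t distribution with d = 0.5.
- Type I error of the test that ignores closed groups: 2 × [1 − Φ(1.96 / √DE)].

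**Results.** The ICC values are assumptions.

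| ICC | DE | 128 / DE | Power of a valid 5% test | Type I error, groups ignored |
|---|---|---|---|---|
| 0 | 1.00 | 128.0 | 80.1% | 5.0% |
| 0.01 | 1.03 | 124.4 | 79.0% | 5.3% |
| 0.02 | 1.06 | 121.0 | 77.9% | 5.7% |
| 0.05 | 1.15 | 111.8 | 74.6% | 6.7% |
| 0.10 | 1.29 | 99.2 | 69.5% | 8.4% |

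Worked example at ICC 0.05: DE = 1 + 2.9 × 0.05 = 1.145, 1.96 / √1.145 = 1.83, and the two-sided tail area is 6.7%.

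**Check by simulation.** The set-up was 16 closed groups of six or seven per arm, 107 patients per arm, a random 64 per arm retained, and an unadjusted two-sample test (20,000 runs). The type I error was 4.9%, 5.7%, 7.0% and 9.0% at ICC 0, 0.02, 0.05 and 0.10, in line with the formula.

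**Relation to the planned test.** The table concerns the single twelve-month contrast, whereas the planned test looks at all time points jointly. A simulation of that likelihood ratio test (random intercept and slope, 64 per arm, closed-group effect only after baseline, assumed variances, 3.9 completers per closed group, 1,500 runs per setting) gave 5.5% at ICC 0.02 and 6.5% at ICC 0.05. The size is similar and the direction the same.

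**The case against.** **The ICC may be small.** The outcome is a postal self-report on daily activities twelve months after discharge, long after the group has dispersed. At ICC 0.01 the cost is about one point of power and 0.3 points of type I error, which nobody would act on. This stands. A reader might infer that power is certainly overstated and that the type I error certainly exceeds 5%. The documents do not support that without a condition, because they give no ICC.

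**The power loss may be offset.** If d = 0.5 refers to the unadjusted standard deviation, baseline adjustment brings a gain that the calculation did not use. With an assumed baseline correlation of 0.5, the effective size becomes 128 / (DE × 0.75), and power is about 86% at DE 1.15 and 81% at DE 1.29. This also stands, but for power only. A gain in precision does not repair a standard error that omits a source of variance.

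**The worst cases are not the plan.** It is tempting to compute with full groups of twelve, or to treat one therapist throughout as a further fixed cluster in both arms. Twelve is a cap, the planning average is six to seven, and filling groups with non-study patients would lower the number of study patients per group. Therapist continuity is explicit for BET but only for the most part in BMR generally. A replacement therapist is foreseen and the number of therapists is not given. Therapist clustering may add to the problem, but the documents do not allow it to be sized. Nor can all 65 therapy hours be taken as shared, since schedules may be individually tailored and BET includes self-directed exercise.

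**Simultaneous starts.** At one centre a control and an intervention group begin together, so effects of the arrival wave are shared between the arms. That removes wave effects from the contrast there, but not the effect of the closed group itself.

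**This is a condensed article.** A fuller protocol or analysis plan might contain a group term. But the article does not leave the structure open: it names the random effects, the test and a finished power calculation, and these do not fit the delivery it describes.

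**Conclusion.** The point holds in conditional form. The design creates closed groups nested in arm, and the stated sample size and model both assume independence. For any positive within-group ICC, the primary interaction test is too liberal, and power is lower than the same calculation with clustering ignored. Over an assumed ICC of 0.01 to 0.10 with 3.9 completers per closed group, the type I error is 5.3% to 8.4% and power 79% to 69%. The effect is negligible at the low end and material from about 0.05. The figures rest on the assumed ICC, on the plan's average group size and 40% loss, and on reading the random terms as patient level. Whether power really falls below 80% stays open because of baseline adjustment. The type I error point does not depend on that.

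**What to change.** 1. Record the closed-group ID and the therapist ID for every study patient. IDs not captured during delivery may be hard to recover later.
2. Add to the primary and secondary models a random effect for closed group that can act on post-baseline change, not only a constant shift over all four assessments.
3. Keep the likelihood ratio test coherent by including this term in both the full and the null model. Alternatively, replace that test explicitly by an F test with Kenward-Roger or Satterthwaite degrees of freedom, which suits roughly 16 closed groups per arm.
4. Report a model with therapist as an added level as a sensitivity analysis.
5. Restate the power for the planned 214 patients over an ICC range (the table above gives 79.0% to 69.5% for 0.01 to 0.10), and say whether d = 0.5 refers to the unadjusted or the baseline-adjusted standard deviation.

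The cost is two ID variables, some model wording, slightly wider intervals and a less favourable stated power. No additional patients are needed.
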